###### Physical Activity Level (Subjective)

The level of physical activity at home is assessed by a validated parent-reported questionnaire [40], after translation into Persian and cross-cultural adaptation [35].

###### Physical Activity Level (Objective)

Pedometers are used for this purpose. Cost, memory capacity, and use burden for children (weight, size, probability of child manipulation, and falling), as well as accuracy and validity, are considered for the selection of pedometers, based on McClain and Tudor-Locke’s suggestion [41]. For this purpose, we use Omron HJ­320 Tri­axis pedometer at baseline and after the intervention. Further to its reasonable price, Omron HJ­320 has several advantages to be used in children. It locates on child’s waist, which is the body axis and gives a better estimation of the physical activity level. Furthermore, it has a 7-day memory and records the number of steps during 7 consecutive days. It is very light (45 g), easy to both set and use, and impossible for child’s manipulation. All pedometers are set based on children’s average length of steps.

##### Quality of Life

Quality of life measures are increasingly being used as an index of population health status after the constitution of the WHO on the definition of “Health” that is a state of complete physical, mental (including emotional and cognitive), and social well-being [42].

We use the Pediatric Quality of Life Inventory 4.0 questionnaire, for children (age 5-7 years) for this purpose [43,44], which has a previously validated Persian version [45] and contains 23 items encompassing 4 fields of children function—physical, emotional, social, and school—and is answered in a 5-point Likert scale.

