To address the challenge of childhood obesity and the double burden of malnutrition in a developing country, we decided to calibrate and customize HSDS as a health promotion initiative, which is now successfully running in 2 provinces in Canada [26]. “Iran Healthy Start (IHS)/Aghazi Salem, Koodake Irani” is the customized Iranian version of Canadian HSDS health promotion program, which is now being developed in Mashhad University of Medical Sciences (MUMS; Mashhad, Iran) and focuses on improving physical activity and healthy eating among preschool children. The principles of IHS are adapted from the original Canadian HSDS, considering unique conditions that exist in the Iranian culture, preschool education bylaws, curriculum, and environment.

Study objectives.To customize and implement the health promotion program (Iran Healthy Start), aligned with preschool bylaws in IranTo determine whether Iran Healthy Start program can:Increase physical activity level and attraction to physical activity among preschoolersReduce sedentary behaviors at home among preschoolersImprove anthropometric parameters in preschoolers toward healthy weightsImprove quality of life in preschoolersImprove eating habits and nutrition risk among preschoolersTo evaluate the feasibility, attrition rate, as well as facilitators and barriers for implementing this program in Iranian preschoolsTo calibrate measurement tools: validating the Persian translation of Nutrition Screening Tool for Every Preschooler and Children Attraction toward Physical Activity

From our point of view, some characteristics of HSDS make it more relevant to what we need. The key characteristic of HSDS is that it is based on evidence-based ecological framework [27] and adheres to the population health approach. Furthermore, it introduces strategies for all levels of influence. Another advantage of this program is its multicultural nature, which makes the program more relevant at the international stage and makes the customization easier, although it requires fundamental modifications to be feasible for Iranian preschool children. HSDS targets all children, regardless of their weight or risk of obesity, which is the primary prevention initiative (health promotion) in the public health approach. This level of prevention includes fundamental activities that are directed at reducing the risk of exposure to a risk factor in an individual or the population [28].

Textbox 1 shows the objectives of this study.

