##### Participants and Data Collection

In the Iranian preschool bylaws, preschool is not a mandatory level, and all children aged 4-6 years can be registered either in preschool-1 (age, 4-5 years) or preschool-2 (age, 5-6 years). All children aged 4-6 years of the selected classes of each center are included in the study after a valid consent from their parents or legal guardian, while those with known chronic disease, such as cardiovascular, respiratory, endocrine, or musculoskeletal problems—after physician inquiry—as well as those who need to adhere to a specific diet, such as gluten-free or phenylalanine-free diets, are excluded.

Data reflecting the nutrition status, diet quality, physical activity and sedentary behaviors, quality of life, and anthropometry of children, as well as the general sociodemographic status of participants and their families are collected at baseline and after the intervention is completed (Table 3). Data collection is performed by a team of 4 nutritionists who are given comprehensive training to standardize the data collection. They learned how to consistently obtain anthropometric measurements, fill the required questionnaires, and train the use of pedometers and filling the parent-report questionnaires to parents. Data entry is done by one person for consistency (a PhD student). Each preschool takes about 7-10 days to collect all the required data. As parents’ cooperation is very important in the data collection, aiming to acknowledge their cooperation, especially in control preschools, a gift for children and a free nutrition consultation for children and their parents, as well as a comprehensive report for child growth, nutrition, and activity status, are dedicated.

As this is a pilot study and we cannot estimate the attrition rate, there is no need to define the sample size, but sample characteristics represent the population of preschool children in Mashhad.

**Table 3 table3:** Overview of the study process.

Group and action		Months	

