###### Nutrition Risk

The NutriSTEP [33,34] has been first designed and validated in Canada in different languages for assessing eating habits and nutrition problems in children aged 3-5 years. A license was obtained from the developers of NutriSTEP questionnaires. The Persian version of NutriSTEP was used after translation and cross-cultural adaptation [35]. The NutriSTEP scoring system categorizes children into low, medium, and high risk in terms of nutritional status. It covers 4 main domains related to children’s food intake as follows: (1) food and fruit intake; (2) physical growth and development; (3) factors affecting the food intake and eating behavior; (4) physical activity and sedentary behavior.

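### The only quality-of-life form named is for ages 5-7 but ages 4-6 are enrolled, so 4-year-olds are measured below its stated range; older children may also fall outside NutriSTEP's

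*Protocol article*

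**What the plan says.** Under Participants and Data Collection, the protocol article sets eligibility by age: "All children aged 4-6 years of the selected classes of each center are included in the study". The same section says that children are "registered either in preschool-1 (age, 4-5 years) or preschool-2 (age, 5-6 years").

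The Quality of Life section names a single instrument: "We use the Pediatric Quality of Life Inventory 4.0 questionnaire, for children (age 5-7 years) for this purpose". It adds that a Persian version had been validated before, but gives no validation below age 5 and no other form for younger children.

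The Nutrition Risk section describes NutriSTEP as designed and validated in Canada for "assessing eating habits and nutrition problems in children aged 3-5 years". It then says: "The Persian version of NutriSTEP was used after translation and cross-cultural adaptation". The study objectives in the Introduction include "validating the Persian translation of Nutrition Screening Tool for Every Preschooler and Children Attraction toward Physical Activity", and the Results section reports that validation paper as submitted. The article does not state the age range of the Persian version.

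Table 4 schedules both tools at baseline and end. Study Design describes a 6-month intervention in 3 intervention and 3 control centers, with 2 classes drawn at random per center. It states no stratification of that draw by preschool level. Data Analysis plans t and chi-square tests between groups, paired t and McNemar tests within groups, and analysis of covariance for covariates that it does not list.

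**The concern.** The stated population is not covered by the stated quality-of-life form, and may not be covered by the nutrition-risk tool. Two things follow.

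1. **Validity.** A score from a child younger or older than a tool's stated range has no support in the article, whichever arm the child is in.
2. **Age-related movement.** Over 6 months some children age into the 5-7 form, and some may age out of the 3-5 tool. If scores shift with age for that reason, a before-after test within one arm cannot separate the shift from a program effect. A between-arm comparison is exposed only if the arms differ in age mix. That can happen by chance with 6 classes per arm and a draw not stated to be balanced on level.

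Quality of life and nutrition risk are both named in the study objectives, so this bears on conclusions that the trial intends to draw.

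**Working it through.** The article gives no sample-size or power figure for these outcomes, so there is nothing to reproduce. The check compares the age ranges and then sizes the overlap under assumptions.

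**Inputs from the article.** Enrolment 4-6 years; preschool-1 is 4-5 and preschool-2 is 5-6 (Participants and Data Collection). Quality-of-life form 5-7 (Quality of Life). NutriSTEP 3-5 in its Canadian version (Nutrition Risk). About 6 months between measurements; 6 classes per arm (Study Design). 152 + 148 = 300 children (Data Analysis).

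**Assumptions.** Let s be the share of children in preschool-1. Ages are uniform within each level, and preschool-1 is read as ending at the fifth birthday. The article gives no value for s, so the full range 0 to 1 is shown.

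**Quality of life: share under 5**
- Baseline: s. At s = 0.5 this is 50%, or 150 of 300; range 0-100%.
- End: s × (1 − 0.5). At s = 0.5 this is 25%, or 75 of 300; range 0-50%.

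**NutriSTEP: share above the range, if the 3-5 limit carried over to the Persian version**
- Range read as ending at the fifth birthday. Baseline: 1 − s = 50% (150), range 0-100%. End: 0.5s + (1 − s) = 75% (225), range 50-100%.
- Range read as including all 5-year-olds. Baseline: 0%. End: 0.5 × (1 − s) = 25% (75), range 0-50%.

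**Where age-related movement enters.** Let d1 and d2 be the mean 6-month drift in score for preschool-1 and preschool-2 without the program, δ the program effect, and p_I and p_C the preschool-1 shares in the intervention and control arms.
- Within the intervention arm, mean change = δ + p_I·d1 + (1 − p_I)·d2. The drift stays in.
- Between arms, difference in change = δ + (p_I − p_C)(d1 − d2). The drift cancels when the arms have the same level mix, or when both levels drift alike.
- If end scores are compared instead, (d1 − d2) is replaced by the difference in mean end score between the two levels without the program.

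**How large p_I − p_C could be.** With equal class sizes, each extra preschool-1 class in one arm shifts the preschool-1 share by 1/6 (17 percentage points) and mean age by about 0.17 year. If each of the 12 classes is independently as likely to be one level as the other (assumption):
- P(arms differ by at least one class) = 1 − 924/4096 = 77%.
- P(arms differ by two or more) = 1 − (924 + 2 × 792)/4096 = 1 − 2508/4096 = 39%. Two classes correspond to 33 percentage points and about 0.33 year.

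**Cost of restricting to children aged 5 or over.** At s = 0.5 this keeps 150 of 300. Under the same independent draw, a center has probability 0.25 of two preschool-1 classes, so P(at least one of 6 centers contributes no child) = 1 − 0.75^6 = 82%.

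The article gives no values for d1, d2 or the level means, so the bias itself cannot be computed.

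**The case against.** The strongest reply is that the trial has a concurrent randomized control. Both arms use the same tools at the same times and age by the same 6 months. A reader might infer that score movement with age would be mistaken for a program effect. For the between-arm comparison the article does not support that as a general statement, because the average drift cancels. Nor does it show that either score drifts with age. What remains is the within-group tests and chance imbalance in class level.

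A reader might also infer that every preschool-1 child is out of range, or that many children are. The first depends on reading 4-5 as stopping at the fifth birthday, and the second on an age mix that is not reported. For NutriSTEP, 3-5 belongs to the Canadian tool. The Persian version has its own validation, which may cover older children, so that part is conditional.

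Age handling and the covariate list are commonly left to a fuller plan, and the planned analysis of covariance could include age. That is fair, and the absence of an age rule is not itself the point. The choice of form is different: the article states it, and the stated range excludes part of the stated population.

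Finally, making the in-range children the main analysis would drop about half the randomized children under the even-split assumption and could empty some centers. That objection stands and shapes the fix.

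**Conclusion.** The concern holds in limited form. As written, 4-year-olds are given a quality-of-life form below its stated age range and no alternative is named. Whether older children fall outside NutriSTEP depends on the age range of the Persian version, which the article does not give.

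With an even split of levels and uniform ages, about half the children are under 5 at baseline and a quarter at the end. Without those assumptions the ranges are 0-100% and 0-50%. The effect on the arm comparison is the product of a chance imbalance in level and a difference between levels in drift or mean score; neither is known. The within-group tests have no such protection. This is a measurement and interpretation problem for two outcomes of a pilot. It does not invalidate the randomized comparison.

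**What to change.** The Results section says that the intervention is complete and the analysis under way, so a different form for the younger children is no longer possible in this trial. The following use data already collected:

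- Keep all children in the main between-arm comparison of quality of life and NutriSTEP, and adjust both models for baseline age in months.
- Report the numbers in preschool-1 and preschool-2 by arm.
- State the age range for which each Persian version was validated.
- Add an analysis limited to children within each tool's range, fixed in writing before the arms are compared: aged 5 or over at baseline for quality of life, and the range validated for the Persian version for NutriSTEP. If arm results have already been seen, label it as post hoc.
- Base conclusions on between-arm differences and treat the paired t and McNemar results as descriptive.
- If the all-children and in-range quality-of-life analyses disagree, limit the conclusion to children aged 5 or over.

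The cost is a few sentences of analysis wording and one extra analysis per outcome. The in-range analysis will be less precise, by an amount that depends on the class mix, and some centers may contribute few or no children to it. It therefore supports the all-children comparison and should not replace it.

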##### Qualitative Interview With Parents, Educators, and Managers

We ask educators to write their comments about the feasibility, attraction, useful hints, and suggestions for increasing children’s and parents’ motivation to actively participate in the program, read the resource, and attend the training sessions during the intervention. After the intervention is completed, we have an in-person interview with managers, educators, and a number of parents to figure out some qualitative data regarding the feasibility of the program in Iran preschools education environment, as well as strengths and limitations of the program in components, materials, and implementation aspects. Parents in the intervention group are stratified to 4 strata, based on the portion of the book they were supposed to read during 6 months—(1) <25%; (2) 25%-50%; (3) 50%-75%; and (4) >75%. Then, 10 parents are randomly selected from each stratum and are contacted through a phone call, and qualitative data regarding the fluency, practicality, usefulness, comprehensiveness, and the potential barriers causing a lack of parental cooperation are collected.

##### Data Analysis

Descriptive analysis (frequency, percentage, mean, and SD) will be used to characterize and compare the basic characteristics of participants in the intervention and control groups. Outcomes related to nutrition and physical activity will be compared between the intervention and control groups to seek any possible improvements following the intervention. Considering the number of intervention (n=152) and control (n=148) participants, which anticipates a normal distribution, independent sample *t* test, and chi-square tests will be used for between-group comparisons, while paired sample *t* test and MacNemar tests will be used for analyzing within-group changes. Any possible covariates will be controlled with the analysis of covariance test. All tests are 2-tailed, and a significance level of <.05 will be considered statistically significant. Data analysis will be done by IBM SPSS Statistics for Windows, version 23.0 (IBM Corp).

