#### Development of the Evaluation Plan

##### Study Design

The evaluation of the IHS program is designed as a pilot randomized controlled trial. For recruitment, officially registered preschools in the Provincial Education Department database are stratified according to the socioeconomic status of people living in that area. The three levels of high, middle, and low socioeconomic areas are defined according to the categorization of the Provincial Education Department. Two preschools are randomly selected from each socioeconomic level (a total of 6 centers) and then allocated to the intervention and control groups (Figure 1). Overall, 3 centers in the intervention group (each center belongs to a different socioeconomic level) and 3 centers in the control group are defined. The selected centers are contacted in person and provided with comprehensive information. After confirmation of managers, 2 classes are randomly selected for enrollment (6 classes in the intervention group and 6 classes in the control group). Then, the parents of eligible children are invited in a meeting in preschool, and informed consent is obtained after a brief introduction on the whole program and the role of parents (for parents of the intervention group) and informing parents for data collection and cooperation in filling questionnaires (for parents of the control group). The components of the intervention program for managers, educators, children, and parents are conducted in intervention classes, and control classes receive the conventional preschool education program. Aiming to acknowledge the cooperation of control preschools, the wait-list approach is suggested to the managers to receive the intervention in the next educational year, as well as a comprehensive report for growth, nutrition, and physical activity status of each child, which is given after the intervention, is completed.

The intervention lasts for 6 months. The duration of an educational year in preschools in Iran is the same as elementary schools and lasts for 8 months (October-May). From March 21, there are around 2-week New Year (Norouz) holidays. The intervention will be completed before Norouz holidays. The required data are collected at baseline and after the completion of the intervention period.

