## Discussion

Developing societies need to have a health promotion program that can overcome the double burden of malnutrition. This requires both overnutrition and undernutrition prevention strategies to be combined and integrated into education and health systems. The IHS program has the potential of a comprehensive health promotion program for young children whose lifestyle behaviors can be modeled and improved toward a healthy future life. The IHS program is developed and customized considering several criteria. Looking at the preschool bylaws in Iran, there is not a systematic rule or program or guideline targeting optimal nutrition or structured physical activity for preschool children. Except for some preschools in the capital city (Tehran), almost all preschools are part-time and do not serve lunch for children. Breakfast and snack are routinely up to the parents, but in some preschools, especially in higher socioeconomic areas, a hot meal is served as breakfast or snack, but not lunch. Regarding the physical environment, usually there are 20-30 children in a preschool class, and the area of classes is usually around 12-15 m^2^, with a small yard where around 10-15 children can safely play. Except for rural preschools, most urban centers do not have adequate space for children to even play or have moderate-to-vigorous physical activities. It is mandatory for preschool educators to teach training books in 2 volumes for preschool children during the educational year, which are developed by the Provincial Education Department and are aligned with the conventional educational objectives in the preschool bylaws, which are briefly titled as follows: (1) training physical and movement skills; (2) training emotional attitude and behaviors; (3) training intellectual skills; (4) training moral and social behaviors; (5) developing fondness for learning the Holly book (Quran); (6) training art and beauty; (7) increasing religious tendency; (8) training national identity; (9) training language skills; (10) promoting health and safety level; and (11) familiarity with the nature and conserving the environment. However, there are not any developed and designed activity units focusing on healthy nutrition and structured physical activity in the bylaws.

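### Six whole preschools are allocated 3 v 3, but the plan tests about 300 children as if they were independent, so its p-values are too small

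*Protocol article*

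**What the plan says.** Under Study Design, the protocol article sets the unit of allocation: "Two preschools are randomly selected from each socioeconomic level (a total of 6 centers) and then allocated to the intervention and control groups". The result is three against three: "Overall, 3 centers in the intervention group (each center belongs to a different socioeconomic level) and 3 centers in the control group are defined". Classes are then sampled within each centre: "2 classes are randomly selected for enrollment (6 classes in the intervention group and 6 classes in the control group". The programme is delivered to whole classes; its components "are conducted in intervention classes, and control classes receive the conventional preschool education program". At no stage is a child allocated individually.

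Under Data Analysis, the choice of tests rests on the number of children: "Considering the number of intervention (n=152) and control (n=148) participants, which anticipates a normal distribution". It follows that "independent sample *t* test, and chi-square tests will be used for between-group comparisons". ANCOVA is added for any covariates, and all tests are two-tailed at .05. The article mentions no centre or class effect, no mixed model or GEE, no centre-level comparison, and no ICC or design effect. It calls the design a pilot randomized controlled trial and does not use the word cluster.

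**The concern.** Children in the same preschool share educators, daily activity sessions, classroom space and neighbourhood. One outcome, the attraction-to-activity questionnaire, is also administered by their own educators. Their outcomes are therefore likely to be correlated. A difference between two centres at the same socioeconomic level that has nothing to do with the programme falls entirely into the treatment contrast. The replication behind that contrast is six centres, whereas the planned standard error is computed from 300 children.

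The argument from sample size to normality does not help. It concerns the shape of the distribution, while the assumption that fails is independence.

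The consequences go beyond the pilot. The objectives ask whether the programme improves activity, anthropometry, eating habits and quality of life. The results are to go to the Ministry of Health as a step towards national implementation. If the stated significance level does not hold, ordinary differences between centres can be reported as programme effects. Any interval built on the same standard error and passed to a larger trial would be too narrow.

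**Working it through.** The article gives no sample-size or power calculation to reproduce. The figure that can be checked is its nominal two-sided level of .05.

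**Inputs from the article**
- Children: 152 + 148 = 300 (Data Analysis).
- Centres: 6, three per arm; classes: 12, six per arm (Study Design).
- Mean cluster size, derived: 300/6 = 50 per centre and 300/12 = 25 per class. This agrees with the Discussion: "usually there are 20-30 children in a preschool class".

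**Assumed input.** The ICC is not in the documents. The one that matters is the residual ICC between centres within a socioeconomic level, taken here as 0.005 to 0.10. Extra correlation within classes was not added.

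**Formulas**
- Design effect: DE = 1 + (50 - 1) × ICC
- Effective sample size: 300/DE
- True type I error of the planned t test: 2 × [1 - Φ(1.968/√DE)], where 1.968 is the t critical value on 298 df
- Ratio of a valid 95% interval width to the child-level one: √DE × t(df)/1.968, with t = 4.303 on 2 df (centres compared within socioeconomic level) or 2.776 on 4 df (level ignored)

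| Assumed ICC | DE | Effective N | Type I error, formula | Type I error, simulated | Width ratio, 2 df | Width ratio, 4 df |
|---|---|---|---|---|---|---|
| 0.005 | 1.25 | 241 | 0.078 | not run | 2.4 | 1.6 |
| 0.01 | 1.49 | 201 | 0.107 | 0.105 | 2.7 | 1.7 |
| 0.02 | 1.98 | 152 | 0.162 | 0.164 | 3.1 | 2.0 |
| 0.05 | 3.45 | 87 | 0.289 | 0.301 | 4.1 | 2.6 |
| 0.10 | 5.90 | 51 | 0.418 | 0.426 | 5.3 | 3.4 |

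The simulation used 10,000 runs per ICC, with centre sizes 51, 51, 50 v 50, 49, 49 and no socioeconomic effect. At ICC 0 the planned t test held its level (0.050). A t test on the six centre means (4 df) stayed between 0.046 and 0.054 at every ICC tried.

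**Interval width at ICC 0.05**
- Child-level standard error: √(1/152 + 1/148) = 0.1155 SD; half-width 1.968 × 0.1155 = 0.23 SD.
- With clustering: 0.1155 × √3.45 = 0.2145 SD. On 2 df the half-width is 4.303 × 0.2145 = 0.92 SD. On 4 df it is 2.776 × 0.2145 = 0.60 SD, which applies only if socioeconomic level has no effect on the outcome.

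**Difference detectable with 80% power**
- Children treated as independent: (1.96 + 0.84) × 0.1155 = 0.32 SD.
- Centre-level, 2 df (noncentral t): 0.80, 0.92, 1.21 and 1.59 SD at ICC 0.01, 0.02, 0.05 and 0.10.

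**Randomisation test.** With one centre per level in each arm there are 2³ = 8 possible allocations, so the smallest two-sided p is 2/8 = 0.25. Were allocation unrestricted (20 ways), it would be 2/20 = 0.10.

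**The case against.** - **It is a pilot.** True, and the article declines a sample-size calculation for that reason. But the same article asks whether the programme works and tests this at .05, so the label does not excuse the tests.
- **Stratification and ANCOVA deal with it.** Having one centre per level in each arm balances differences between levels. It leaves differences between centres within a level, which are confounded with treatment. Child-level covariates do not restore centre-level replication, and centre cannot be entered as a fixed covariate because it is nested in arm.
- **A fuller analysis plan may exist.** That would answer an omission. Here the article names the tests and justifies them by the child counts.
- **The size is assumed.** This stands. At ICC 0.005 the error rate is about 8%, inflated but not grossly. Residual ICCs may be small for some outcomes after baseline adjustment, and clustering is less certain for outcomes that arise mainly at home. Socioeconomic variation would also enlarge the child-level standard error and somewhat lower the error rates in the table.
- **Confidence intervals are not promised.** Correct: the section names only tests. The point about intervals follows from the same standard error.
- **The 0.25 floor applies only to a randomisation test.** Also correct. A model-based centre-level analysis can give a smaller p under its distributional assumptions. The fair statement is that three against three centres gives very little power and a weak basis for significance claims.

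**Conclusion.** The concern holds: the article fixes an analysis that is invalid for its own allocation scheme, and this affects every between-group test it plans. Over assumed within-level ICCs of 0.01 to 0.10, with 50 children per centre, the nominal 5% error becomes about 11% to 42%. Even the low end doubles it. The exact inflation depends on ICCs that only the trial data can supply, and these will differ by outcome. That the tests ignore the unit of allocation does not depend on the ICC. The article says the intervention is complete and analysis is under way, so the correction belongs before any results are released.

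**What to change.** Replace the child-level t, chi-square and ANCOVA comparisons with an analysis at the unit of allocation:

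1. **Centre-level analysis.** Compute baseline-adjusted centre means (or proportions), take the three within-level differences, and use t on 2 df. This is the simplest analysis that matches the design.
2. **Alternative.** Fit a linear or generalised mixed model with socioeconomic level as a fixed effect, random centre and class, and small-sample degrees of freedom. Large-sample GEE, or a mixed model without such a correction, is not reliable with six centres.
3. **Reporting.** Give each effect as an estimate with its 95% interval and the estimated ICC, which is what a definitive trial will need. State that three centres per arm give little basis for claims of significance.
4. **Description.** Call the study a cluster randomised pilot under Study Design.

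The cost is revised wording and a different procedure on data already collected. Intervals will be about 2.7 to 5.3 times as wide as the child-level ones (2 df, ICC 0.01 to 0.10), and few effects are likely to reach .05. That reflects what six centres can show.
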